## Abstract

**Background:**

Implementing community health nursing programs is a new field of application in the primary health sector of Germany. Hence, there is limited evidence of effective community-based and nurse-led interventions with regard to the German health care system. International research findings are mostly not transferable. The Community Health Nursing in der Stadt (CoSta; ie, “Community Health Nursing in the City”) project is the first study that examines a community health nurse–led intervention for adults with chronic health conditions.

**Objective:**

This study protocol describes the design and methods of a randomized controlled field trial that will investigate if a community health nurse–based intervention has an impact on health-related quality of life in adults with chronic conditions.

**Methods:**

The study was designed as a randomized controlled trial that will be conducted under real-life conditions in the field. In a 4-month period, patients with at least 1 chronic *International Classification of Diseases, Tenth Revision*, diagnosis will be enrolled. Participants will be randomly allocated to an intervention group or a control group. The sample size was assumed based on an effect size of 0.50 with a significance level of .05, using a 2-sided (2-tailed), 2-sample unequal variance *t* test. The control group will be treated as usual. The intervention group will receive—in addition to the usual treatment—preventive home visits; consultations; and educative training, which will be offered by 2 community health nurses for up to 12 months. Both groups will be followed up at baseline, after 6 months, and after 12 months. The primary outcome measure is the mental component summary score from the 36-Item Short Form Health Survey after 12-months. Secondary patient outcomes will be included. The study received ethics approval from the Competence Health Center’s institutional review board at the University of Applied Sciences Hamburg (procedure number: 2020-14).

**Results:**

The CoSta project was funded by the Federal Ministry of Education and Research Germany (contract number: 13FH019SX8). In total, 187 participants were recruited at the beginning of August 2021. Further, 92 were excluded and 94 were randomized. Data collection will be conducted until the end of 2022.

**Conclusions:**

Our study will provide data with regard to the effectiveness of community nurse–led interventions that focus on the treatment of vulnerable adults with chronic health conditions in a community health center. In secondary analyses, the associations among influencing social factors (education, income, and employment) will be examined. We expect results that will help reduce the research-to-practice gap.

**Trial Registration:**

German Clinical Trials Register DRKS00026164; https://tinyurl.com/yckxc5ut

**International Registered Report Identifier (IRRID):**

DERR1-10.2196/37965

## Introduction

### Background

The implementation of advanced nursing professionals in primary care has become a topic of public debate in Germany lately. The COVID-19 pandemic has emphasized already existing gaps and health inequalities in primary care and community settings. During the last 2 years, different studies reported a disproportionate impact on disease burden and well-being in vulnerable target groups, as well as socioeconomic disparities resulting from the pandemic event [1,2]. Neighborhoods with high rates of poverty, precarious employment, and discrimination are more affected by COVID-19 itself and the economic, psychological, and social consequences resulting from the pandemic [3]. Additionally, for people with (multiple) chronic health conditions, a higher risk of experiencing these effects, as a result of the pandemic event, has been reported [4]. Regional data on reported COVID-19 cases in Germany show increased mortality rates in socially disadvantaged districts [5], references to COVID-19–related outcomes (eg, infection rates), and correlations with social indicators [6]. The latest evidence does not differ from those reported in previous pandemics [7], revealing existing health-related inequity in societies [8] and underlining the important roles of community and public health services and authorities. In Germany, this evidence has intensified the discourse on gaps in the health care system. It is not news that primary care is under threat, particularly as there is a lack of health services in certain rural and urban districts that exacerbates unequal access, especially among socially disadvantaged populations [9]. Moreover, it is well known that there is a gap in life expectancy (up to 10 years between high-income and low-income individuals) in Germany. These differences also exist for the majority of people with chronic health conditions. Such health inequalities are largely the result of social determinants of health [10]. Therefore, using nurse-centered approaches in the community could be a sustainable solution. According to successfully implemented international role models, the community health nursing (CHN) concept [11] has been discussed for the primary health sector in Germany [12,13]. Nurse professionals at the master's degree level provide evidence-based care and health promotion in various settings (eg, in community health centers [CHCs]), addressing vulnerable groups and their particular needs [14]. The initiative of the Robert Bosch Foundation (with the Agnes Karll Society and the German Professional Association of Nursing) to establish CHN and test master's degree programs in Germany [13], as well as a recently published legal requirement [15], has advanced this ongoing debate. In other countries, such as Canada, this nurse profile has been implemented in health services for several years [16]. However, international research findings are mostly not directly transferable to the German health care system. The legal framework for CHN's scope of action is still lacking [13], and funding for CHN and CHN’s anchoring in the laws on benefits must be reviewed [13]. Accordingly, CHN still needs to be developed in Germany, and more information and evidence are needed about the effectiveness of community-based nurse interventions and their impact on socially determined health inequalities. The CHN in der Stadt (CoSta; ie, “Community Health Nursing in the City”) project is the first project that evaluates CHN interventions for patients with chronic health conditions who live in a disadvantaged neighborhood (Hamburg-Veddel). The social disadvantages that many residents experience in this neighborhood manifest as high unemployment rates, low household incomes, and a high dependence on state transfer payments, when compared to other districts of the city [17]. Furthermore, health challenges are reflected in the neighborhood by both the higher prevalence of chronic conditions, such as hypertonus, and the low utilization of outpatient care [18].

The CoSta project was funded in 2020 by the German Federal Ministry of Education and Research. For the project, a community nurse–led care concept targeting chronic conditions has been developed. The research questions of the CoSta study aim at exploring how community health nurse interventions impact health-related quality of life, health literacy, coping, depressive symptoms, anxiety, social participation, and the utilization of health services among patients with chronic health conditions. Furthermore, we assume that social disadvantage will correlate with the impact on chronic health conditions and the use of health care services. In the secondary analyses, we will focus on the effects of education, employment, and income on health. To answer the research questions, a randomized controlled trial (RCT) will be conducted for 1 year. The CoSta project is being realized via a joint effort by the University of Applied Sciences Hamburg and Community Health Centre Policlinic Veddel. Statistical advice has been provided by the Institute of Medical Biometry and Epidemiology at the Medical Center Hamburg-Eppendorf. The purpose of this study protocol is to describe the RCT, which was designed to examine the effectiveness of a new community health nurse concept among adults with chronic health conditions. This study protocol follows the SPIRIT (Standard Protocol Items: Recommendations for Interventional Trials) guidelines.

### Objectives

The aim of the CoSta study is to explore the effects of a new nurse health care concept on patients with chronic health conditions (ie, effects on primary and secondary outcome measures) and compare them to the effects of usual treatment. The primary alternative hypothesis is that participants in the intervention group will experience greater improvements in the mental components of their health-related quality of life compared to those experienced by participants in the control group over a 12-month period. The following research questions will be addressed in secondary analyses:

How do the outcomes of patients regarding health-related quality of life, depressive symptoms, anxiety, health literacy, coping, social participation, and the utilization of health care differ between groups (nurse-led intervention group and usual care group)?How should nurse-led consultations be designed?How can nurse-led health promotion interventions be implemented in the neighborhood?

## Methods

### Trial Design

The CoSta study was designed as a prospective, monocentric, 2-armed RCT that will evaluate the effectiveness of community nurse–led interventions for adults with chronic conditions from an urban area in Germany. A 1:1 allocation ratio for the intended number of participants in each of the two groups will be used. The primary and secondary outcomes that will be assessed in the study are guided by the principle that defines *health* as “a state of complete physical, mental and social well-being and not merely the absence of disease or infirmity,” as stated in the Constitution of the World Health Organization [19]. The methodological procedure is based on the methods of a Canadian study that evaluated an interprofessional, nurse-led program for promoting self-management in older adults with multiple chronic conditions [20]. A participant timeline recommended by the SPIRIT guidelines was generated to visualize the planned process of enrollment, interventions, and selected validated assessment instruments (Multimedia Appendix 1).

### Study Setting

The study will enroll adult patients with chronic health conditions who are treated in a CHC and will involve a multiprofessional team of general practitioners, clinical psychologists, social workers, midwives, and advanced nurses who provide health care in the community. The clinic is located in the Hamburg-Veddel district, which can be described as a socially disadvantaged urban neighborhood wherein about 5000 people live in a densely built housing estate surrounded by railroad tracks, highways, and a port and industrial area. The residents are comparatively young, and many are dependent on state transfer payments [17]. Chronic health conditions, such as diabetes mellitus, hypertension, heart failure, and lung diseases, are highly prevalent [18]. Further, the amount of primary care offerings are comparatively below the average. Interprofessional cooperation will play a great part in developing the program. The two interventionists have their own office, and both participate in interprofessional case conferences and supervision meetings.

### Eligibility Criteria

The criteria that were chosen will allow for the broad inclusion of current patients with chronic diagnoses from the CHC. Participants who fulfill the following criteria will be enrolled: (1) patients who provide informed consent, (2) patients aged ≥18 years (no limit), (3) patients who are registered as patients at the CHC, (4) patients with a diagnosis of at least 1 chronic condition, and (5) patients who live at home.

Patients who do not fit the criteria for the study, refuse to participate, or are experiencing a severe course of disease will be excluded. Furthermore, people living with dementia or an acute psychiatric diagnosis and patients living in foster care will be excluded from enrollment.

### Interventions

The framework of the CHN concept is based on the “critical-emancipatory concept of nursing action” [21]. The CoSta program is a 12-month, patient-driven, multicomponent intervention that was developed to empower patients with chronic health conditions in managing their illness. It consists of the following three different types of nurse-led interventions: (1) home visits offered once per month by the community health nurse, (2) weekly consultations offered by the community health nurse, and (3) monthly training sessions that are tailored to the course of a chronic disease and are hosted by specialist practitioners or the interventionists themselves. During the home visits and consultations, assessments, physical examinations, and care coordination and planning will be carried out by the community health nurse. During the weekly consultations, assessments, care coordination and care navigation (linking participants to other health care services) will be conducted by the community health nurse. During 4 additional topic-centered consultation hours (each will occur once per month), which will be dedicated to cardiovascular diseases, lung diseases, chronic pain, and diabetes mellitus, as well as specific disease counseling, will be offered. Professional translators will be brought in for the interventions, as needed.

Patients who are randomly assigned to the intervention group will be offered all of the aforementioned interventions in addition to the usual treatment that they receive in the CHC. The interventionists will not deliver any health services to participants who are randomly assigned to the control group. These participants will be offered treatment as usual. Because the CHN concept involves patient-tailored interventions, the content of the interventions will differ among participants to some degree due to individual patient needs and the course of the health condition.

### Outcomes

The surveys will take place at baseline (t_0_), after 6 months (t_1_), and after 12 months (t_2_). The primary patient-reported outcome of the study is the mental dimension of the health-related quality of life items (mental component summary [MCS] score; 12 items) from the 36-Item Short Form Health Survey (SF-36), which will be measured as changes in MCS scores from t_0_ to t_2_. We will use the self-report SF-36 questionnaire, which includes retrospective questions about the previous 4-week period. The SF-36 includes 36 questions regarding subjective health status. It has been psychometrically tested and normed for Germany [22,23]. For secondary patient-reported outcomes, the following instruments will be used: (1) the physical dimension of the health-related quality of life items (physical component summary score; 12 items) from the SF-36 [22,23]; (2) the summary score of depression scale from the Patient Health Questionnaire-9 [24]; (3) the short form of the German version of the European Health Literacy Survey Questionnaire (HLS-EU-Q47; HLS-EU-Q16-GER [includes 16 items from the HLS-EU-Q47]) [25]; and 6 scales from the HLS-EU-Q47 [26], Index for the Assessment of Health Impairments [27], and Essen Coping Questionnaire [28].

### Participant Timeline

Multimedia Appendix 1 shows the timeline of study phases, as recommended by the SPIRIT guidelines, for the enrollment, intervention, and assessment time points.

### Sample Size

A power analysis was done a priori. The sample size was calculated with the Power Analysis & Sample Size 16.0.3 program (NCSS LLC) to demonstrate group differences in the primary outcome (MCS scores). The assumptions were based on a study by Markle-Reid et al [20]. The sample size was estimated based on an effect size of 0.50 with a significance level (α) of .05, using a 2-sided (2-tailed), 2-sample unequal variance *t* test (experimental group sample size: mean 55.3, SD 7.8; control group sample size: 53.5, SD 9.6). The maximum number of cases was limited to 130 in order to guarantee that the interventions will be offered to every participant in the intervention group during the limited study period. This maximum sample size of 130 (65 per group), which was calculated based on the aforementioned input parameters, yields 64.1% power to reject the null hypothesis.

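### The stated 64.1% power follows from neither planning effect in the Sample Size section: the printed means and SDs give d = 0.21 and about 21%, an effect size of 0.50 gives about 81%

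*Protocol article*

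**What the plan says.** The Sample Size section of the protocol article describes a single a priori calculation for the primary outcome, the SF-36 mental component summary (MCS) score. The test is given as "using a 2-sided (2-tailed), 2-sample unequal variance" t test at a significance level of .05. Two descriptions of the effect follow. One is standardised: "The sample size was estimated based on an effect size of 0.50". The other is a pair of group values: "experimental group sample size: mean 55.3, SD 7.8" and "control group sample size: 53.5, SD 9.6".

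The total was capped at 130, 65 per group, by the capacity to deliver the intervention. This number, "which was calculated based on the aforementioned input parameters, yields 64.1% power to reject the null hypothesis".

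The section mentions no dropout allowance, baseline correlation or other adjustment. It says that the assumptions were based on a cited study, without saying which quantities were taken from it. The Abstract repeats the standardised effect only: "The sample size was assumed based on an effect size of 0.50 with a significance level of .05".

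**The concern.** For a two-sample t test, the group means, the SDs, the group size and alpha together determine both the standardised effect and the power. The section prints all of these and adds an effect size and a power. The printed means differ by 1.8 points against SDs of roughly 8 to 10, which is nowhere near half a standard deviation. So at least one of the effect size and the group values cannot be what was used, and the power may match neither.

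This is the article's only statement of what the trial was sized to detect. A planning difference of 1.8 MCS points and one of 4.4 points are very different targets. A reader who later has to interpret a non-significant primary result needs to know which was meant.

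**Working it through.** **Inputs, all from the Sample Size section:** n = 65 per group; two-sided alpha 0.05; unequal-variance (Welch) t test; means 55.3 and 53.5; SDs 7.8 and 9.6; effect size 0.50; stated power 64.1%.

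**Step 1. Effect size implied by the printed values.**
- Difference: 55.3 − 53.5 = 1.8.
- Root-mean-square SD: √((7.8² + 9.6²)/2) = √(153.00/2) = 8.746.
- d = 1.8/8.746 = 0.206. Standardising by one SD alone gives 1.8/7.8 = 0.231 or 1.8/9.6 = 0.188. None is near 0.50.
- Conversely, d = 0.50 corresponds to 0.50 × 8.746 = 4.37 points.

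**Step 2. Attempt to reproduce 64.1%.** Power comes from the non-central t distribution with Satterthwaite degrees of freedom.
- Standard error: √(7.8²/65 + 9.6²/65) = √(153.00/65) = 1.534.
- Degrees of freedom: about 122.9; critical value 1.979.
- Non-centrality = difference/1.534.

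| Effect used | Difference | Non-centrality | Power at 65 per group |
|---|---|---|---|
| Printed means and SDs | 1.80 | 1.173 | 21.4% |
| Effect size 0.50 | 4.37 | 2.850 | 80.7% |
| Solved to give 64.1% | 3.59 (d = 0.41) | 2.339 | 64.1% |

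The normal approximation gives 21.6% and 81.3% for the first two rows, so the method of calculation is not the explanation. The stated figure is 64.1 − 21.4 = 42.7 percentage points above the first and 80.7 − 64.1 = 16.6 below the second.

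**Step 3. Could a standard variant explain it?**
- One-sided test at 5%: 31.6% (printed means) or 88.3% (d = 0.50).
- 130 per group with the printed means: 38.0%.
- Effect of 0.50 standardised by one SD only: 71.3% (SD 7.8) or 87.4% (SD 9.6).
- d = 0.50 with attrition: 64.0% at 44 per group, a loss of 1 − 44/65 = 32%; a 30% loss gives 65.0%. No attrition is stated.
- Baseline adjustment (ANCOVA, assumed correlations 0.3 to 0.8): 23% to 50% with the printed means, 85% or more with d = 0.50.

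No variant that keeps the two-sided 5% level, 65 per group and either stated effect reaches 64.1%.

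**Step 4. Group sizes that the two effects would require under this t test.** For 1.8 points, 64.1% power needs about 256 per group and 80% needs about 372. For d = 0.50, 80% needs 64.

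**Step 5. The same calculation at the number enrolled.** The Results section reports 94 randomized, so about 94/2 = 47 per group under 1:1 allocation. The standard error becomes √(153.00/47) = 1.804. Power before dropout is 16.7% for 1.8 points and 66.9% for d = 0.50.

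**The case against.** The best defence is that this is a misprint in a condensed article. A difference of 3.6 points would give 64.4%, so one wrong mean or SD could account for much of the mismatch. That may be so. But the article does not let the reader tell which number is wrong, and it ties the power explicitly to the inputs that it prints. An adjustment set out in an unseen document would not make that sentence true.

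It is also fair to say that the error leaves the outcome, the randomization and the analysis model untouched, that recruitment is closed, and that the article already discloses power below 80%. All of that stands. It limits the remedy to a correction of the record and does not make the figures compatible.

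A reader might go further in three ways that the article does not support.
- **That the cited study showed an effect of only 0.21.** The section says only that the assumptions drew on that study. It does not present the group values as that study's observed result. What can be said is that the printed values imply 0.21.
- **That the trial has 21% power, so a null result is to be expected even if the intervention works.** The Statistical Analysis section plans a mixed model with baseline values as covariates. With an assumed baseline correlation of 0.8, a baseline-adjusted comparison would reach about 50% for 1.8 points at 65 per group. The 21% belongs to the stated t test and holds only if the true difference is 1.8.
- **That the section contradicts itself on whether 130 was calculated or capped.** The sentence before the power statement makes clear that it was a cap. The later clause most naturally refers to the power and is only badly placed.

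**Conclusion.** The point holds as an arithmetic inconsistency and should be corrected. With 65 per group and a two-sided 5% unequal-variance t test, the two effect inputs disagree (0.50 against 0.21). The stated power matches neither: it is about three times what the printed means and SDs deliver (64.1/21.4 = 3.0) and about 17 points below what 0.50 delivers. It would need a difference of roughly 3.6 points, twice the printed 1.8.

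The conclusion rests only on the section's own inputs and on the absence of any stated adjustment. It does not establish which figure is wrong, and it does not measure the power of the planned mixed model.

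**What to change.** Recover the original output of the sample-size software. From it, state the difference, SDs, effect size and power actually used as one consistent set in the Sample Size section, make the Abstract agree, and correct or delete whichever figure is wrong. According to what the output shows:
- if the printed means and SDs stand, restate the effect size as 0.21 and the power as about 21%;
- if 0.50 stands, restate the power as about 81% and justify 0.50 against printed values that imply 0.21;
- keep 64.1% only if the difference of about 3.6 points behind it is stated.

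Because 94 participants were randomized, add what the chosen inputs give at about 47 per group before dropout, labelled as the t-test calculation. As a minor wording change, describe 130 simply as the capacity limit at which power was evaluated.

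The cost is one recalculation and a few sentences. No extra patients are needed and the design does not change, though the stated power may turn out less favourable.
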